### Outcome measures

#### Primary outcome measure

The primary outcome measure is change in cognition from baseline to 12 months, assessed by Montreal Cognitive Assessment (MoCA, v7.2) [31], in the standard and low temperature dialysis groups.

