### Data analysis

Data analysis will be performed by statisticians who are blinded to participant treatment allocation. A mixed method approach will be used, utilising semi-structured interviews, questionnaires and measurement of cognitive function. The 12 month follow-up period will be the key assessment time for all outcomes. Normally distributed data will be presented as mean (SD), skewed data as median (IQR) and categorical data as number (percent). The main aim of the qualitative component is to assess issues related to patient recruitment. This will include practicalities of implementing cooler dialysate, adherence to treatment, effectiveness of blindness process and identification of factors that may affect routine practice of treatment in various centres. We will apply thematic analysis to qualitative data collected from semi-structured interviews. Interviews will be on a 1:1 basis and will be audio-recorded. They will be transcribed by the research assistant and will be anonymised and securely stored, accessible only by the research team. The purpose of the quantitative analysis is to estimate the mean and standard deviation for MoCA at baseline and follow-up in both trial arms and obtain an estimate of the attrition. For all analysis, the level of significance will be set at 5%, so that 95% confidence intervals will be presented. This is a feasibility study and statistically or clinically significant changes in outcomes between groups are unlikely; hence, no between-group inferential comparisons will be made. However, a preliminary estimate of a treatment effect is relevant to sample size estimation of future definitive trials. As an exploratory analysis, we will conduct a complete case analysis of the primary and secondary outcomes. A linear regression model will be used for continuous outcomes (e.g. MoCA) and a logistic regression model will be used for binary outcomes. Each model will include the baseline measurement and treatment arm as independent variables. All patients randomised to their respective study arms will be included in the intention to treat analysis. Missing data, if any, will be managed using the last-observation carried forward approach. There will be no interim analysis of the data, though the safety data resulting from any SAE will be collated and made available to the Trial Steering Committee. All analysis will be conducted in Stata 15.

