### Sample size

The outcome data from this feasibility study will be used to inform the sample size calculation for the definitive trial, by providing estimates of the primary outcome and its variability and the expected attrition. The study aims to recruit a total of 90 patients from four sites. Lancaster and co-workers outlined the key aspects of feasibility studies and indicated at least 30 patients per each arm are required to identify the sample variability (standard deviation) in key variables to enable the calculation of power for testing hypotheses in subsequent definitive studies [46]. The primary outcome in the definitive study is likely to be a value from the MoCA. With 45 patients in each arm, and if the mean (SD) value of the MoCA is 27 (2) in the control and intervention arms at the study start, we could expect a 95% confidence interval to range from 26.4 to 27.6 in each arm. This will give adequate precision for the estimate required in the study. With 45 patients in the control arm, and assuming a mean (SD) value of MoCA of 22 (3) after 12 months, we could expect a 95% confidence interval to range from 21.1 to 22.9. In the intervention arm, assuming a mean (SD) MoCA value of 25 (3) after 12 months, we could expect a 95% confidence interval to range from 24.1 to 25.9. Furthermore, with a total sample size of 90 patients, with an expected loss of 20% of the patients, a 95% confidence interval could be produced, ranging from 70.2 to 87.7%.

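### Carrying the last observation forward as the general missing-data rule would bias the 12-month MoCA means and SDs under the plan's own assumed decline, and the plan does not say which rule yields the reported figures

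*Protocol article*

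**What the plan says.** All of the analysis rules stand in one paragraph of the protocol article, under Data analysis.

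- Purpose: "The purpose of the quantitative analysis is to estimate the mean and standard deviation for MoCA at baseline and follow-up in both trial arms", together with an estimate of attrition. The paragraph rules out between-group inferential comparisons but adds that "a preliminary estimate of a treatment effect is relevant to sample size estimation of future definitive trials".
- Complete cases: "As an exploratory analysis, we will conduct a complete case analysis of the primary and secondary outcomes". The linear and logistic models follow directly: "Each model will include the baseline measurement and treatment arm as independent variables".
- Analysis set: "All patients randomised to their respective study arms will be included in the intention to treat analysis".
- Missing data: "Missing data, if any, will be managed using the last-observation carried forward approach". The sentence is not tied to an outcome, a summary or a model.

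The outcome itself is defined under Primary outcome measure: "The primary outcome measure is change in cognition from baseline to 12 months", on the MoCA. The Blinding section and Table 1 schedule the MoCA at 0, 6 and 12 months. The Sample size section takes 27 (SD 2) at baseline in both arms, 22 (SD 3) at 12 months in control, 25 (SD 3) at 12 months in the intervention arm, and an expected loss of 20% of 90 patients. For control at 12 months it states that "we could expect a 95% confidence interval to range from 21.1 to 22.9".

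**The concern.** Carrying the last score forward treats a patient as unchanged from the last visit to month 12. The study is built on the opposite premise, that MoCA declines, and its planning values have control declining faster than intervention. A score carried from baseline or month 6 is then higher on average than the missing 12-month score would have been, and by more in control. This holds even when who is lost has nothing to do with cognition.

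What is at stake is the main quantitative product of the study. The follow-up mean and SD by arm, and possibly the preliminary effect, are meant to size a definitive trial. A mixture of 12-month scores and earlier scores estimates none of these at 12 months. In addition, two missing-data rules cover the same outcomes, and nothing says which one produces the numbers to be handed on.

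**Working it through.** **Inputs from the Sample size section:** baseline 27 (SD 2) in both arms; 12 months 22 (3) in control and 25 (3) in intervention; 45 per arm; 20% loss.

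**Assumptions not in the document:** loss completely at random and equal by arm unless stated; 6-month means midway, 24.5 in control and 26.0 in intervention, with SD 2.5; two-sided 5% and 80% power for the later trial. The plan gives no timing of loss, so the results are shown as a range between two extremes: everyone lost has a 6-month score, or no one has.

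**1. The plan's own intervals.** Mean ± 1.96 × SD/√45:
- baseline 27 ± 0.58 = 26.4 to 27.6
- control at 12 months 22 ± 0.88 = 21.1 to 22.9
- intervention at 12 months 25 ± 0.88 = 24.1 to 25.9

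All agree with the stated limits. The 12-month intervals use all 45 patients per arm although 20% are expected to be lost. The exact binomial interval for 72/90 retained is 70.2 to 87.7%, also as stated.

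**2. Mean and SD after carrying forward.** With loss d, 12-month values m and s, and carried values m₀ and s₀:

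mean = (1−d)m + d·m₀; variance = (1−d)s² + d·s₀² + d(1−d)(m−m₀)².

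At d = 0.2:

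| Carried score | Control mean | Control variance (SD) | Intervention mean | Intervention variance (SD) | Difference |
|---|---|---|---|---|---|
| None | 22.0 | 9 (3.0) | 25.0 | 9 (3.0) | 3.0 |
| 6-month | 0.8×22 + 0.2×24.5 = 22.5 | 7.2 + 1.25 + 1.0 = 9.45 (3.07) | 0.8×25 + 0.2×26 = 25.2 | 7.2 + 1.25 + 0.16 = 8.61 (2.93) | 2.7 |
| Baseline | 0.8×22 + 0.2×27 = 23.0 | 7.2 + 0.8 + 4.0 = 12.0 (3.46) | 0.8×25 + 0.2×27 = 25.4 | 7.2 + 0.8 + 0.64 = 8.64 (2.94) | 2.4 |

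Half of each gives control 22.75, intervention 25.3 and difference 2.55. On the change scale, control goes from −5.0 to between −4.5 and −4.0, and intervention from −2.0 to between −1.8 and −1.6.

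**3. If carried-forward data enter the baseline-adjusted regression.** Simulation of 4,000 trials with half of each kind of loss and assumed visit correlations of 0.5 and 0.7 gave an adjusted difference of about 2.55 with carried-forward scores and 3.0 with complete cases.

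**4. Size of a later trial read from these figures.** n per arm = 2(1.960 + 0.842)² × pooled variance / difference² = 15.7 × pooled variance / difference²:
- none: 15.7 × 9/9, so 16
- 6-month carried: 15.7 × 9.03/7.29 = 19.4, so 20
- baseline carried: 15.7 × 10.32/5.76 = 28.1, so 29

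**5. Unequal loss (assumed rates, baseline carried).**
- 30% control, 10% intervention: 25.2 − 23.5 = 1.7
- 10% control, 30% intervention: 25.6 − 22.5 = 3.1

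The true difference is 3.0, so the bias has no fixed direction.

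**6. Interval half-widths.** Complete cases, 36 per arm: 1.96 × 3/√36 = 0.98, giving 21.0 to 23.0 and 24.0 to 26.0. With carried-forward scores counted as 45 per arm:
- control: 1.96 × 3.07/√45 = 0.90 (6-month carried) or 1.96 × 3.46/√45 = 1.01 (baseline carried)
- intervention: about 0.86 in both cases

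**The case against.** The strongest reply is that this is a feasibility study. Its progression criteria are recruitment, attrition and compliance, none of which depends on how missing MoCA scores are filled. The values of 22 and 25 are introduced conditionally to illustrate precision, and the plan itself thinks important between-group changes unlikely. The article is also condensed. That limits the consequences, but it does not remove the point: the rule is stated outright and without restriction, and it acts on the means and SDs that the plan names as the purpose of the quantitative analysis.

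Four stronger readings are tempting, and the text does not support them.

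- *A reader might infer that the plan contradicts itself.* The complete-case analysis is labelled exploratory and can stand beside a separate intention-to-treat analysis with carried-forward scores. What is missing is a statement of which one supplies the reported figures.
- *A reader might infer that the effect estimate is certainly biased.* The only models described come straight after the complete-case sentence. If they use complete cases only, the carried-forward rule never reaches them. The rule follows later in the paragraph without restriction, so both readings are open.
- *A reader might take an 1.8-fold larger later trial (29 against 16 per arm) as the expected consequence.* That needs every lost patient to have no 6-month score and the biased data to enter the model. With 6-month scores carried the figure is 20.
- *A reader might say that the intervals become too narrow.* Compared with complete cases this is not general: with baseline carried, the control interval is slightly wider (1.01 against 0.98). The firmer objection is that filled-in scores are counted as observed and the centre of the interval is moved.

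**Conclusion.** The concern holds for the descriptive results. Under the plan's own decline and 20% random loss, carrying scores forward raises the control 12-month mean by 0.5 to 1.0 point, compared with the plan's own half-width of about 0.9. It raises the intervention mean by 0.2 to 0.4. The SD is distorted mainly in control (up to 15% too large) and by only about 2% in the intervention arm.

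For the arm difference the conclusion is conditional. Only if carried-forward data enter the regression does the difference fall to 2.4–2.7 under equal loss, and under unequal loss it can err either way.

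The sizes rest on the plan's illustrative values, on the assumed 6-month scores and, for the later trial, on the assumed 80% power. With a smaller real decline the bias in the means shrinks in proportion. The feasibility criteria are untouched.

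**What to change.** In the Data analysis section:

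1. Remove last observation carried forward as the default.
2. Report MoCA means and SDs from observed scores, with n for each visit and arm.
3. Estimate the preliminary arm difference from a likelihood-based repeated-measures model on the scores already scheduled at 0, 6 and 12 months, with baseline MoCA, age group (the stratification factor), arm, visit and arm-by-visit. Say that this is the estimate to be carried into the definitive trial's sample size.
4. Keep the complete-case regression as a sensitivity analysis, labelled as such.
5. Tabulate deaths and transplants by arm, and do not impute cognitive scores after them.

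The cost is a change of wording and a little more analysis work; no new data are needed. The 12-month summaries will rest on about 36 patients per arm, with intervals of about 21.0 to 23.0 and 24.0 to 26.0 on the planning values, instead of the stated intervals based on 45. Observed means remain unbiased only if loss is unrelated to cognition. The model needs the weaker condition that loss depends on observed data.

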### Sample size

The outcome data from this feasibility study will be used to inform the sample size calculation for the definitive trial, by providing estimates of the primary outcome and its variability and the expected attrition. The study aims to recruit a total of 90 patients from four sites. Lancaster and co-workers outlined the key aspects of feasibility studies and indicated at least 30 patients per each arm are required to identify the sample variability (standard deviation) in key variables to enable the calculation of power for testing hypotheses in subsequent definitive studies [46]. The primary outcome in the definitive study is likely to be a value from the MoCA. With 45 patients in each arm, and if the mean (SD) value of the MoCA is 27 (2) in the control and intervention arms at the study start, we could expect a 95% confidence interval to range from 26.4 to 27.6 in each arm. This will give adequate precision for the estimate required in the study. With 45 patients in the control arm, and assuming a mean (SD) value of MoCA of 22 (3) after 12 months, we could expect a 95% confidence interval to range from 21.1 to 22.9. In the intervention arm, assuming a mean (SD) MoCA value of 25 (3) after 12 months, we could expect a 95% confidence interval to range from 24.1 to 25.9. Furthermore, with a total sample size of 90 patients, with an expected loss of 20% of the patients, a 95% confidence interval could be produced, ranging from 70.2 to 87.7%.

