### Study setting and population

Patients will be recruited through the renal clinics at four HD units in the United Kingdom at Birmingham Heartlands Hospital, Runcorn Road Renal Unit, Solihull Hospital and Castle Vale Renal Unit. All these HD units are under the collective organisation of the University Hospitals Birmingham NHS Foundation Trust. The study aims to recruit 90 patients allocating 45 patients in the intervention and 45 patients in the control group. Suitable patients will be identified by the direct care team. The care team will speak with the suitable patients to see if they are happy to have their details passed on to the research team for further discussion. If the patient agrees, the research team will contact the patient and determine eligibility. Suitable patients will be identified through searching records in the four participating units. An information pack will be given to the patient (see Additional file 1), who will be given 24 h to read the information and ask any questions they may have. The research team will then contact the patient, in a pre-agreed manner (i.e. next clinic visit, via telephone) to see if they have any further questions or would like to participate in the study. If they would like to participate in the study they will arrange to meet and complete the consent form (see Additional file 2).

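### The interval printed for 20% loss is the interval for 80% retention, the 12-month MoCA intervals ignore that loss, and the planning means conflict with the claim that significant differences are unlikely

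*Protocol article*

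**What the plan says.** All the planning figures are in the Sample size section of the protocol article.

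- **Size.** "The study aims to recruit a total of 90 patients from four sites". Study setting and population adds the split, "allocating 45 patients in the intervention and 45 patients in the control group". The section also cites a minimum of 30 per arm for estimating variability.
- **Baseline MoCA.** With mean 27 and SD 2, "we could expect a 95% confidence interval to range from 26.4 to 27.6 in each arm". The remark that precision is adequate comes directly after this interval.
- **12-month MoCA, control.** The stated condition is 45 patients with mean 22 and SD 3, and for that case the section says "we could expect a 95% confidence interval to range from 21.1 to 22.9".
- **12-month MoCA, intervention.** With mean 25 and SD 3, the interval given is 24.1 to 25.9.
- **Loss.** "with an expected loss of 20% of the patients, a 95% confidence interval could be produced, ranging from 70.2 to 87.7" (percent). The sentence does not name the quantity that the interval describes, and gives no time point.

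The Data analysis section says that "the level of significance will be set at 5%, so that 95% confidence intervals will be presented". It makes 12 months the key assessment time and names attrition and MoCA (mean and SD) as the quantities to be estimated. It plans an exploratory complete case analysis, and last observation carried forward for missing data. It explains the absence of inferential between-group comparisons by saying that "statistically or clinically significant changes in outcomes between groups are unlikely".

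**The concern.** Three things in these two sections do not fit together.

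1. The only proportion named in the loss sentence is 20%, and the interval attached to it does not contain 20%.
2. The 12-month intervals use every randomised patient, although the same paragraph expects one in five to be lost.
3. The planning means describe a large treatment difference, while Data analysis gives the unlikelihood of a significant difference as its reason for making no comparisons.

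Twelve-month MoCA and attrition are what the trial sets out to estimate for the definitive study. A reader who takes the printed figures at face value gets the wrong interval for loss, a slightly optimistic precision at 12 months, and two incompatible accounts of the effect the investigators expect.

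**Working it through.** **Inputs.** 90 patients, 45 per arm (Sample size; Study setting and population). Means (SD) of 27 (2) at baseline, and 22 (3) and 25 (3) at 12 months; expected loss 20% (Sample size). Two-sided 5% level (Data analysis).

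**Step 1: reproduce the MoCA intervals.** Half-width = t(0.975, n − 1) × SD / √n. With n = 45, t = 2.015.

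- Baseline: 2.015 × 2/√45 = 0.60, giving 26.4 to 27.6. This matches.
- 12 months, control: 2.015 × 3/√45 = 0.90, giving 21.1 to 22.9. This matches.
- 12 months, intervention: the same half-width, giving 24.1 to 25.9. This matches. The section does not restate n for this arm, but 45 reproduces the printed interval and 36 does not.

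**Step 2: apply the expected loss.** 45 × 0.80 = 36 per arm. With n = 36, t = 2.030 and the half-width is 2.030 × 3/√36 = 1.015.

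| 12-month MoCA | n = 45 (printed) | n = 36 |
|---|---|---|
| Control, 22 (3) | 21.1 to 22.9 | 21.0 to 23.0 |
| Intervention, 25 (3) | 24.1 to 25.9 | 24.0 to 26.0 |
| Half-width | 0.90 | 1.02 |

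The ratio is 1.015/0.901 = 1.13, so the intervals are about 13% wider, or 0.11 MoCA points on each side.

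**Step 3: identify the loss interval.** Expected loss is 0.20 × 90 = 18, so 72 are retained. Exact (Clopper-Pearson) 95% intervals:

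- 72/90 = 80% retained: 70.25% to 87.69%. This matches the printed limits.
- 18/90 = 20% lost: 12.31% to 29.75%, that is 12.3% to 29.8%.

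The normal, Wilson (with and without continuity correction), Agresti-Coull and Jeffreys intervals for 72/90 do not match the printed limits. The printed interval is therefore the exact interval for retention.

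**Step 4: compare the planning means with the statement on likely effects.** The difference is 25 − 22 = 3 points, and 3/3 = 1 SD. The standard error of the difference is 3 × √(2/n).

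- n = 45: 0.632, so the difference is 3/0.632 = 4.7 standard errors.
- n = 36: 0.707, so the difference is 3/0.707 = 4.2 standard errors.

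A two-sided 5% two-sample comparison has about 99.7% power at 45 per arm and about 98.7% at 36 (98.9% by the normal approximation). If the planning values held, a significant difference would be close to certain.

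**The case against.** The strongest reply is that nothing has been miscalculated. That stands: all four intervals reproduce from their own inputs, and the control interval is stated on the condition of 45 patients. A reader might infer that the precision figures as a whole are wrong, and the documents do not support that. What is wrong is a label, a sample size that ignores the stated loss, and a clash of assumptions.

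Other stronger readings also fail.

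- **That these intervals alone justify 90 patients.** The section also cites a minimum of 30 per arm, which 36 still meets.
- **That the claim of adequate precision falls.** It follows the baseline interval, which later dropout does not touch.
- **That the mislabelled interval conceals something.** Loss is 100% minus retention, so a reader who spots the slip recovers 12.3% to 29.8% at once.
- **That the corrected interval undermines the attrition criterion because it contains 20%.** An interval around an observed 20% contains 20% at any sample size. The criterion in Secondary objectives also applies at 6 months, whereas the 20% in Sample size has no time point.

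It can also be said that carrying the last observation forward keeps 45 per arm. It keeps 45 rows, but not 45 observed 12-month scores, and the planning SD of 3 is given for scores at 12 months. The complete case analysis would have about 36 per arm in any event.

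Finally, the width of an interval depends on the SD and n, not on whether the mean is 22 or 25, so the effect inconsistency is not a precision error. That is right, and it is treated here as a separate matter. The means may have been meant only as illustrations, but the section does not say so.

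**Conclusion.** The concern holds as a minor matter of labelling and consistency.

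- The interval attached to 20% loss belongs to 80% retention; the one for loss is 12.3% to 29.8%.
- The 12-month intervals are right for 45 per arm but do not allow for the loss expected in the same paragraph. At 36 per arm the half-width is 1.02 instead of 0.90, a small change.
- The planning means imply a 1-SD difference with about 99% power, which contradicts the reason given in Data analysis for making no comparisons. Forgoing comparisons is sound in a feasibility trial; only the stated reason fails.

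The figures for 36 per arm assume that the 20% loss applies to 12-month MoCA and falls equally on the two arms. The documents state neither. The power figures assume a common SD of 3 and a simple comparison of 12-month means.

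**What to change.** 1. State the loss interval as 12.3% to 29.8%, or keep 70.2% to 87.7% and label it as retention.
2. Restate the 12-month intervals for 36 per arm: 21.0 to 23.0 (control) and 24.0 to 26.0 (intervention). Leave the baseline interval as it is.
3. Rest the decision to make no between-group comparisons on the trial's feasibility purpose rather than on significant changes being unlikely; or mark the means of 22 and 25 as illustrative only.

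The cost is a few reworded sentences and slightly less favourable stated precision. Recruitment and the planned analyses do not change.
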